**Fasting Blood Sample**

Following a 10 hr overnight fast on the initial screening visit and 72 hr post training, we will obtain a fasting plasma and serum sample by venupuncture (8ml).

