**I) Initial Screening Visit**

Before subjects formally enter the study, they will be asked to report to the laboratory to ensure they are eligible for participation. During this visit (approximately 45 minutes), subjects will i) read and sign a consent form for the study; ii) conduct a health assessment (questionnaire, height, weight, resting heart rate and blood pressure); iv) provide a fasting blood sample obtained by venupuncture (8ml) and v) complete a physical activity questionnaire.

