**II) Baseline Testing**

Once we determine that subjects have met our inclusion criteria, we will invite them to enter the baseline testing phase of the study. This period will include 4 visits to the laboratory: 1) Insertion of Continuous Glucose Monitor (CGM) and accelerometer (Actiheart) which will be worn for 72 hr; 2) DEXA and skeletal muscle biopsy; 3) A VO_2peak_ test; 4) HIT familiarization to become acquainted with the exercise protocol. Subjects will also be asked to complete at 3 d diet record.

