**V) Post-training Testing**

24-48 hrs following the last training bout we will measure resting blood pressure and HR and insert the CGM and Actiheart which will be worn for the following 48 hr (time of interest will be 48-72 hr post training). 72 hr following the last training session participants will undergo a DEXA scan, skeletal muscle biopsy and fasting blood sample. We will also obtain the CGM and Actiheart at this time. At least 72 hr following the biopsy, participants will report to the laboratory for a VO_2peak_ test.

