**Continuous Glucose Monitoring (CGM)**

In order to assess the effects of i) a single HIT session and ii) 6 wk of HIT on glycemic regulation under free-living conditions, continuous glucose monitoring (CGM) will be employed for a control day during baseline testing (72 hr), during and after the first HIT session (72 hr) and during post-training testing (48 hr). CGM involves inserting a tiny sensor into the subcutaneous tissue of the abdomen which is connected to a continuous glucose measuring device (CGMS iPro, Medtronic, Northridge, CA). In order to standardize the quantity and timing of nutritional intake, subjects will be provided with individualized, standardized diets to consume during the 72 hr monitoring period. Food intake logs will be utilized to ensure compliance with the standardized diet and to verify meal timing. We have employed this technique in our laboratory previously in patients with type 2 diabetes (13,17)

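### The baseline and post-training fasting blood samples are not matched in visit timing or preceding diet, and the single-group paired test counts any effect of that mismatch as training

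*Protocol*

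**What the plan says.** Under Procedures, Fasting Blood Sample, the Protocol names two draws only: "Following a 10 hr overnight fast on the initial screening visit and 72 hr post training". The section on the Initial Screening Visit places the first at the eligibility visit, before the participant formally enters the study.

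Methods, II) Baseline Testing, lists four later visits. The first fits the glucose monitor and activity monitor; the others are "2) DEXA and skeletal muscle biopsy; 3) A VO_2peak_ test; 4) HIT familiarization to become acquainted with the exercise protocol". None includes a blood draw, so the screening sample is the only pre-training value.

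For the post-training draw, Methods, V) Post-training Testing, says "72 hr following the last training session participants will undergo a DEXA scan, skeletal muscle biopsy and fasting blood sample". It adds, of the same visit, "We will also obtain the CGM and Actiheart at this time".

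On diet, the Continuous Glucose Monitoring section says "subjects will be provided with individualized, standardized diets to consume during the 72 hr monitoring period". The same section gives the monitoring lengths as 72 hr at baseline and then "during and after the first HIT session (72 hr) and during post-training testing (48 hr". Dietary and Physical Activity Controls separately asks participants not to change their diet during the training period, checked by 3 d food records before and after.

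The blood outcomes (Data Analysis) are glucose, insulin and free fatty acids. Statistical Analysis applies a paired t-test at 0.05 to all data. There is one group.

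**The concern.** A one-group paired comparison attributes the whole pre-post difference to the intervention. That is defensible only if the two measurements are taken under the same conditions apart from training. Here the fasting blood is separated at baseline from the measurements it accompanies after training. DEXA and biopsy are paired visit for visit ("DEXA and skeletal muscle biopsy" at baseline, and both again at the 72 hr visit), while the baseline blood comes from screening, an unspecified time earlier.

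The Protocol itself treats food intake as something to standardize when glycemic regulation is measured, since it supplies meals for that purpose. If those meals precede one draw and not the other, a diet-related difference in fasting glucose, insulin or free fatty acids would be reported as an effect of the training. Because the mismatch arises at collection, no later analysis can remove it.

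**Working it through.** **1. The two draws side by side**

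| Feature | Baseline draw | Post-training draw |
|---|---|---|
| Visit | Screening, before baseline testing | 72 hr after last session |
| Taken with | Health assessment and questionnaires | DEXA and biopsy |
| Glucose monitor | Not yet fitted | Collected at this visit |
| Overnight fast | 10 hr | 10 hr |
| Diet in preceding days | No control stated | Probably the provided diet; not stated outright |

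The only condition stated to be common to both is the 10 hr fast.

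**2. Does the provided diet precede the post-training draw?** The Continuous Glucose Monitoring section introduces all three monitoring periods together and gives standardized intake as the purpose of the meals. It also uses the monitor to assess six weeks of training, a comparison that would itself be unmatched if only the post-training period lacked the diet. Covering all three periods is therefore the natural reading. Taken literally, however, the diet belongs to a 72 hr period and the post-training period is 48 hr, so the meals might apply only to the other two.

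**3. How long would that diet period be?** Post-training Testing has the monitor fitted 24 to 48 hr after the last session, worn for 48 hr, and collected at 72 hr.
- Fitted at 24 hr: 24 + 48 = 72 hr, which agrees with collection.
- Fitted at 48 hr: 48 + 48 = 96 hr, which is later than collection; only 72 − 48 = 24 hr of wear is available.

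The timings agree only at the early end of the fitting window, so the number of diet days before the draw cannot be read from the Protocol.

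**4. What an unmatched condition would do to the test.** The plan gives no figure of its own to reproduce: no diet effect, and no effect size or SD behind its sample size. The shift is therefore an assumption. Let d be the shift due to the mismatch, in SDs of the paired difference, with no training effect. I take the test as two-sided (the Protocol does not say). The probability of rejecting in the direction of the shift is

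P = Pr(T′ > t(0.975, n−1)), where T′ is noncentral t with n−1 degrees of freedom and noncentrality d√n.

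For n = 20, the planned enrolment with all completing, t(0.975, 19) = 2.093. For n = 16, an assumed number of completers, t(0.975, 15) = 2.131.

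| d | d√20 | P, n = 20 | d√16 | P, n = 16 |
|---|---|---|---|---|
| 0 | 0 | 0.025 | 0 | 0.025 |
| 0.1 | 0.447 | 0.062 | 0.4 | 0.056 |
| 0.25 | 1.118 | 0.185 | 1.0 | 0.153 |
| 0.5 | 2.236 | 0.564 | 2.0 | 0.465 |

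For any non-zero d the rate rises with n, so recruiting more participants does not help.

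**The case against.** The strongest objection is that the diet difference is inferred. A reader might conclude that the post-training draw definitely ends a provided-diet period, that the screening draw reflects habitual eating, and hence that diet is established as confounded with training. The documents do not support that. The meals are tied to a 72 hr period and post-training monitoring is listed as 48 hr; habitual eating before screening follows only from the absence of a stated control; and the meals are described as individualized, without saying how far they depart from usual intake. This stands, and it limits the claim to a probable diet difference.

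It does not dispose of the point. Under the literal reading the baseline sample still comes from a different, earlier visit with no diet condition, and the Protocol is silent on diet before the later draw.

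Second, there are existing controls. The shared 10 hr fast is real standardization, but it fixes the hours since the last meal and not the preceding days' intake. The no-change instruction covers the training period, and its food records are not tied to the screening draw. These reduce the concern without removing it.

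Third, the size is assumed. At 0.1 SD the rate is about 6%, little above nominal, and the documents do not rule out a shift that small or smaller. That also stands.

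Finally, the scope is narrow. Only three blood measures are affected. Glycemic control is also assessed by continuous monitoring, and biopsy and DEXA are placed at corresponding visits. The lack of a control group is common to every outcome; what is particular here is the additional, avoidable mismatch.

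**Conclusion.** The concern holds in limited form. It is certain from the text that the baseline fasting sample is drawn at screening, that no baseline-testing visit repeats it, and that the post-training sample is drawn at a different kind of visit at the end of monitor wear. It is probable, but not stated, that the provided diet precedes only the second draw. In a single-group paired t-test, any effect of these differences on fasting glucose, insulin or free fatty acids is inseparable from training.

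Neither the size nor the direction of that effect can be derived from the documents. The rates of about 6%, 18% and 56% at n = 20 (6%, 15% and 46% at n = 16) rest on assumed shifts of 0.1, 0.25 and 0.5 SD, no training effect, and a two-sided test. They show how sensitive the test is to a shift; they do not estimate the error rate in this trial. The change should be made because it is cheap and the problem cannot be repaired after collection, but it affects the fasting blood measures and not the trial as a whole.

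**What to change.** 1. Take the baseline fasting sample used in the paired comparison during baseline testing, at the end of the baseline monitoring and provided-diet period, after the same number of standardized-diet days as before the post-training draw. One way is to schedule the baseline DEXA and biopsy visit at that point, with participants fasted; the Protocol does not currently say when that visit falls relative to the monitoring, or that it is fasted, so both need stating.
2. In the Continuous Glucose Monitoring section, state that the provided diet covers the post-training monitoring period, and for how long before the draw.
3. Reconcile the fitting, wear and collection times in Post-training Testing, so that the number of diet days can be matched.
4. Use any screening sample for eligibility only.

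The cost is some rescheduling within existing visits and, if the screening sample is kept, one additional small blood draw per participant.

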**Continuous Glucose Monitoring (CGM)**

In order to assess the effects of i) a single HIT session and ii) 6 wk of HIT on glycemic regulation under free-living conditions, continuous glucose monitoring (CGM) will be employed for a control day during baseline testing (72 hr), during and after the first HIT session (72 hr) and during post-training testing (48 hr). CGM involves inserting a tiny sensor into the subcutaneous tissue of the abdomen which is connected to a continuous glucose measuring device (CGMS iPro, Medtronic, Northridge, CA). In order to standardize the quantity and timing of nutritional intake, subjects will be provided with individualized, standardized diets to consume during the 72 hr monitoring period. Food intake logs will be utilized to ensure compliance with the standardized diet and to verify meal timing. We have employed this technique in our laboratory previously in patients with type 2 diabetes (13,17)

**Actiheart**

In order to monitor physical activity levels, participants will wear the Actiheart on 3 occasions while wearing the CGM: for 72hr during baseline testing, 72 hr during training and 48hr during post-training testing. The Actiheart is a compact, chest-worn monitoring device that records heart rate and physical activity. It is non-invasive, weighs less than 10 grams and is waterproof. The Actiheart has two clips which attach directly to standard ECG electrodes. One electrode is adhered at V1 or V2 (4^th^ intercostals) and the second electrode is placed approximately 10 cm to the left at V4 or V5. This placement can be adjusted to be comfortable for the subject (i.e. can be positioned above or below the breasts for females). The number of R-waves detected is recorded in 15, 30 or 60 second epochs. Simultaneously, an internal accelerometer senses the frequency and intensity of the subject’s torso movements. Energy expenditure is calculated from both the HR and activity data.

**Dual X-Ray Absorptiometry (DEXA) Scan**

Body composition will be measured by DEXA (Lunar Prodigy Advance, Madison, WI, USA) before and after training. This is a painless non-invasive procedure that uses a small amount of radiation to assess how much fat, bone, and lean tissue is in the entire body. One trained technician will conduct all scans.

**Skeletal Muscle Biopsy Procedure**

Using standard procedures, muscle biopsy samples will be obtained under local anaesthesia (2% lidocaine) from the *vastus lateralis* several days before, at 6 wk and after training using a Bergstom needle adapted with suction (18). The obtained biopsy samples (~100-150 mg each, wet weight) are immediately dissected from any visible fat or connective tissue, sectioned into several pieces, frozen in liquid nitrogen, and stored at -80ºC until subsequent analysis. For immunohistochemistry, a small piece of muscle (approximately 20mg) will be oriented in cross section, mounted in Optimum Cutting Temperature (OCT) compound (Tissue-Tek, Sakura Finetek, USA) and frozen in isopentane cooled with liquid nitrogen. The mounted samples will be stored at -80°C pending analysis.

**VO_2_peak Test**

Subjects will complete an incremental maximal oxygen uptake (VO_2_max) test on a cycle ergometer (Lode Excalibur Sport V 2.0, Groningen, The Netherlands). A metabolic cart with an on-line gas collection system (Moxus modular oxygen uptake system, AEI Technologies, Pittsburgh, PA) will acquire oxygen consumption (VO_2_) and carbon dioxide production (VCO_2_) data and heart rate will be monitored continuously with a heart rate monitor (Polar A3, Lake Success, NY). Following a 5 min warm-up at 50 watts (W) the resistance will be increased by 1 W every two seconds until volitional exhaustion or the point at which pedal cadence falls below 40 rpm. Heart rate will be monitored continuously throughout the test via telemetry with a heart rate monitor (Polar A3, Lake Success, NY). VO_2peak_ and maximal workload (Wmax) will be defined as the highest oxygen consumption and power output values achieved over a 30 s period. The subject is deemed to have reached VO_2_max if: i) the perceived exertion is >19 (Borg Scale); ii) their HR ± 5bpm of age-predicted maximal HR; iii) their RER is >1.2; and iv) a plateau has been reached in their oxygen consumption.

**Dietary and Physical Activity Controls**

Participants will be instructed to make no changes to their diet over the course of the training intervention, which will be verified by 3 d food records before and after training. Additionally, subjects will be asked to refrain from initiating any other form of exercise into their daily routine.

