**METHODS**

**Subjects**

Twenty men and women (n=10 each) between the ages of 18-45 years will be recruited through poster advertisement.

Inclusion criteria will include:

- Classification of “sedentary” based off a International Physical Activity Questionnaire (IPAQ) score of < 600 MET min/wk
- Body mass index (BMI) > 25/27 < 30kg/m

Exclusion criteria will include:

- Active cardiovascular disease
- Cerebrovascular disease including previous stroke or aneurysm (large vessel or intracranial
- Respiratory disease including pulmonary hypertension of COPD
- Metabolic disease including: parathyroidism, hyper/hypothyroidism, Cushing’s disease or type 1 or 2 diabetes
- Active inflammatory bowel disease
- Renal disease
- Malignancy
- Recent steroid treatment (within 6 mo), or hormone replacement therapy
- Clotting dysfunction
- Musculoskeletal or neurological disorders
- Any disease requiring long-term drug prescriptions, including statins

Details of the experimental protocol, purpose and potential risks of participation will be explained to all subjects and written informed consent will be obtained. Sample size is based on estimated changes in primary outcome variables and standard deviations obtained from analysis of previous studies. 8 subjects are required to detect changes at an alpha level of 0.05 with 80% power. To preserve power we will recruit 10 males and 10 females.

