**STATISTICAL ANALYSIS**

All data will be analyzed using a paired Student’s t-test with significance set at p ≤ 0.05.

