**PERSPECTIVES AND SIGNIFICANCE**

The proposed study will add to the growing body of literature suggesting low-volume HIT is a highly potent and time efficient exercise strategy for improving metabolic health. This will be the first study to assess changes in skeletal muscle oxidative capacity, glycemic control and body composition in overweight individuals following a HIT protocol involving a total time commitment of less than 30 minutes per week. Considering the most commonly cited barrier to regular exercise is a “lack of time” identifying short-duration, high-intensity exercise protocols could be an effective and appealing strategy to improve fitness of the population.

Figure 1. Overview of Experimental Protocol

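### Entry sets no condition on stable weight or current dieting, so a weight trend that predates enrolment may continue and be read as a training effect on fat mass

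*Protocol*

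**What the plan says.** The Subjects section of the Protocol states the recruitment route: "Twenty men and women (n=10 each) between the ages of 18-45 years will be recruited through poster advertisement". It gives two inclusion criteria: "Classification of “sedentary” based off a International Physical Activity Questionnaire (IPAQ) score of < 600 MET min/wk" and "Body mass index (BMI) > 25/27 < 30kg/m". Neither these nor the listed exclusions mention recent weight change or current dieting.

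At the Initial Screening Visit, staff "conduct a health assessment (questionnaire, height, weight, resting heart rate and blood pressure". Weight is taken once there, and no weight-stability condition is attached to it.

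Diet is covered under Dietary and Physical Activity Controls. The instruction reads "Participants will be instructed to make no changes to their diet over the course of the training intervention". The check on whether people followed it is given next: "which will be verified by 3 d food records before and after training".

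The Overview of Experimental Protocol describes a single group that passes through screening, baseline testing, six weeks of training and post-testing, with no control arm or control period. The Statistical Analysis section says "All data will be analyzed using a paired Student’s t-test". Body composition is among the outcomes the study is presented as assessing: "This will be the first study to assess changes in skeletal muscle oxidative capacity, glycemic control and body composition in overweight individuals".

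**The concern.** The diet instruction is meant to remove diet as an explanation for change. It does so only for someone who starts in energy balance, and nothing at entry requires that. A volunteer who is already eating below requirement follows the instruction by going on eating below requirement.

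The food records do not catch this. They ask whether intake changed between two times, and a constant deficit shows no change. This differs from diet drifting during training, which the records could detect.

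Because everyone is trained and the only contrast is after versus before, a weight trend that predates entry adds directly to the estimated mean change. DEXA fat mass is most exposed. Fasting insulin and glucose are exposed less directly, through weight. What is at stake is whether a reduction in fat mass can be credited to the exercise programme.

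**Working it through.** **Plan's own figure.** The protocol gives none for this point. Its sample-size statement (8 subjects, alpha 0.05, 80% power) reports neither an expected change nor an SD, so no SD of fat-mass change can be taken from it.

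**Inputs from the Protocol.** n = 20 (10 men and 10 women); six weeks of training with DEXA before and after; paired t-test at p ≤ 0.05. Sidedness is not stated, and two-sided is assumed.

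**Assumed inputs, none in the documents.**
- True training effect on fat mass: zero.
- About 7 weeks between scans (six of training plus the testing days on either side).
- k entrants already losing 0.25-0.5 kg/wk, 80% of it fat, and continuing at that rate.
- SD of fat-mass change around each person's own trend: 0.8-1.6 kg.
- No entrant gaining weight.

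**Spurious change per affected entrant.** Rate × weeks × fat share:
- 0.25 × 7 × 0.8 = 1.40 kg
- 0.50 × 7 × 0.8 = 2.80 kg

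**Bias in the group mean.** (k/20) × 1.40 to (k/20) × 2.80 kg.

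**Chance of a significant fat loss.** Simulated paired t-test, counting rejections in the direction of loss only, so the nominal rate is 2.5%:

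| Entrants already losing (k) | Mean bias, kg | Chance of false significant loss |
|---|---|---|
| 0 | 0 | 2.5% |
| 1 | 0.07-0.14 | about 3-5% |
| 2 | 0.14-0.28 | about 5-9% |
| 3 | 0.21-0.42 | about 7-17% |
| 4 | 0.28-0.56 | about 9-32% |

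**Hand check of one cell** (k = 4, 1.40 kg each, SD 0.8):
- Expected SD of the 20 changes: √(0.8² + 1.40² × 4 × 16 / (20 × 19)) = √(0.640 + 0.330) = 0.985 kg.
- Standard error: 0.985/√20 = 0.220 kg.
- Mean loss needed for significance: 2.093 × 0.220 = 0.461 kg.
- The mean is centred on a loss of 0.28 kg with SD 0.8/√20 = 0.179 kg, so z = (0.461 − 0.28)/0.179 = 1.01, a tail of about 16%. The simulation gives 18% for this cell.

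**With weight gainers.** Adding entrants who gain at the same rate:
- 3 losing, 1 gaining: about 2-5%
- 3 losing, 2 gaining: below about 3%
- 4 losing, 2 gaining: about 0.3-4%

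The false-positive rate therefore returns to roughly nominal or below. The estimate is less fully protected: with 3 losing and 1 gaining, the net bias is still (3 − 1)/20 × 1.40 to 2.80 = 0.14-0.28 kg. Part of the fall in rejections comes from the wider spread of changes.

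**How tight a stability criterion must be.** A tolerance of 2 kg over 3 months (13 weeks) admits 2/13 = 0.15 kg/wk, or 0.15 × 7 × 0.8 ≈ 0.86 kg of fat per entrant between scans. Three or four entrants at that limit give a bias of 0.13-0.17 kg and a false-positive rate of about 5-11%.

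**The case against.** The strongest case against is that the size rests on inputs the documents do not give. No section says how many poster respondents would be dieting. With one or two such entrants the inflation is small, and a few weight gainers, whom the criteria equally fail to exclude, bring the error rate back to about nominal. That stands: it limits the size and makes the direction uncertain. It does not remove the gap, because nothing ensures that losers and gainers balance.

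A reader might infer several stronger things that the documents do not support:

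- *That anyone already losing weight will go on doing so.* The instruction asks for an unchanged diet and does not fix energy balance. Continuation is possible, not certain.
- *That the bias must favour the intervention.* This holds only if nobody is gaining weight.
- *That CGM results are directly distorted.* The Continuous Glucose Monitoring section supplies individualized, standardized diets during monitoring, so habitual restriction does not feed straight into those readings. Only an indirect route through weight change remains.
- *That the trend can never be seen.* Baseline diet records and Actiheart energy expenditure are both collected, and intake set against expenditure gives a noisy indication of a deficit. It is too imprecise to correct the estimate.
- *That weight history is never asked.* The items of the screening questionnaire are not reproduced. What can be said is that no eligibility condition uses such an answer.

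The activity limit also removes people losing weight through substantial exercise, but not dieters. Finally, the root weakness is the lack of a control group or control period, and this is one of several confounders of that design. That is fair, and it is why the point is a refinement of eligibility rather than a contradiction in the text.

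**Conclusion.** The point holds in a limited form. The eligibility criteria do not require stable weight, the diet check passes a constant deficit or surplus as compliance, and a single-arm paired comparison cannot reliably separate a prior weight trend from training. The exposure is mainly DEXA fat mass, secondarily fasting insulin and glucose, and CGM only indirectly. Only fat mass has been quantified.

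The figures for one to four losing entrants are an illustration. They depend on the assumed rate of loss, fat share, interval, SD and absence of gainers, and the true number of such entrants is unknown. This is a cheap improvement worth making before recruitment, not evidence that the result will be wrong.

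**What to change.** Add to the inclusion criteria in the Subjects section that entrants are not currently following a weight-loss diet and report stable weight over the previous months, with the window and tolerance stated. Ask both at the Initial Screening Visit.

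Choose the tolerance by converting it to kg of fat over about 7 weeks, as in the working. The result should be small against the expected SD of change. By that measure 2 kg over 3 months is loose. A criterion of this kind screens out gainers as well as losers. The instruction to keep the current diet can then stay as written.

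Do not treat agreement between screening weight and baseline DEXA mass as confirmation of stability. The gap between those visits is not stated, and over one week a loss of 0.25-0.5 kg is too small to establish from two readings on different instruments. Use the comparison at most as a coarse flag.

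The cost is one criterion, one or two screening questions, a few more screen failures and slightly slower recruitment of 20 people. Because the criterion relies on self-report, it reduces the bias but does not remove it.
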